## Abstract

**Background:**

The International Myeloma Working Group recommends the use of 18-fluorodeoxyglucose (FDG) positron emission tomography/computed tomography (PET/CT) for treatment response evaluation, as it is superior to magnetic resonance imaging (MRI). However, at initial staging, the sensitivity of FDG-PET remains inferior to that of MRI. Therefore, there is a need for an imaging technique that could have a sensitivity equal to that of MRI at diagnosis and could serve to evaluate therapy. 18F-choline has shown increased sensitivity when compared with 18-FDG, with about 75% more lesions detected in patients with relapsed or progressive multiple myeloma (MM).

**Objective:**

Our primary objective is to prospectively compare the detection rate of bone lesions by 18F-choline PET/CT (FCH-PET) and FDG-PET in newly diagnosed MM. Our secondary objectives are to assess the accuracy of both PET modalities for the detection of bone lesions and the diagnosis of diffuse disease, to assess the detection rate of extramedullary lesions.

**Methods:**

We will prospectively include 30 patients in a paired comparative accuracy study. Patients with de novo MM will undergo FCH-PET, FDG-PET, and whole-body MRI (WB-MRI) within a 3-week period. WB-MRI will be composed of conventional sequences on the spine and pelvis and of whole-body diffusion axial sequences. The following 6 skeletal areas will be defined: skull, sternum/costal grid, spine, pelvis, superior limbs, and inferior limbs. The number of focal lesions, their respective localization, and intensity of uptake will be retrieved for each skeletal area. Readings will be performed blinded from other imaging techniques. The reference standard will be WB-MRI. Focal lesions present on PET/CT but not on WB-MRI will require a decision made with a consensus of experts based on clinical and imaging data. The number of bone lesions and number of extramedullary lesions will be compared using the Wilcoxon test. The accuracy of FCH-PET and FDG-PET will be compared using the McNemar test.

**Results:**

The study started in September 2019, and enrollment is ongoing. As of June 2020, 8 participants have been included. Data collection is expected to be completed in June 2021, and the results are expected to be available in December 2021.

**Conclusions:**

This study will assess if FCH-PET is superior to FDG-PET for the evaluation of MM tumor burden. This will pave the way for future prospective evaluations of the prognostic value of 18-FCH for treatment response evaluation in MM patients. Additionally, this work may provide new perspectives for better assessment of the risk of smoldering MM progressing to MM.

**Trial Registration:**

ClinicalTrials.gov NCT03891914; https://clinicaltrials.gov/ct2/show/NCT03891914

**International Registered Report Identifier (IRRID):**

DERR1-10.2196/17850

## Introduction

Multiple myeloma (MM) is the second most frequently occurring hematological malignancy, with an incidence rate in Europe of 7.4/100,000 men per year and 3.8/100,000 women per year [1,2]. The median age at diagnosis is 69 years [2,3].

MM is defined by the clonal proliferation of more than 10% of malignant plasma cells in the bone marrow associated with signs of myeloma-related organ dysfunction including anemia, hypercalcemia, bone lesions, and renal impairment.

During the past decade, the median overall survival period has almost doubled, from a median of 3 years to 6 years, mainly due to the expansion of the therapeutic arsenal with the use of proteasome inhibitors and immunomodulatory drugs [4]. While the proportion of patients reaching a complete response has increased, the majority of patients eventually relapse. The survival of patients with MM mainly depends on prognostic factors at initial workup. These factors include age, performance status, extramedullary disease, the revised International Staging System stage, cytogenetic abnormalities, and tumor burden [5]. Another important prognostic factor is the depth of the biological response to treatment. This is currently assessed by measuring the level of secreted monoclonal protein in the blood or urine. Complementarily, evaluation of minimal residual disease (MRD) is increasingly performed to finely evaluate patient’s treatment response with the use of multiparameter flow cytometry or next-generation sequencing [6]. However, MRD assessment requires a sample of bone marrow, usually taken from the iliac crests. MRD diagnostic performance can therefore be hampered by the location of residual disease.

Functional imaging such as 18- fluorodeoxyglucose (FDG) positron emission tomography/computed tomography (PET/CT) or magnetic resonance imaging (MRI) can help assess the tumor burden at diagnosis as well as residual disease. Previous studies have shown that 18-FDG PET/CT is superior to MRI for the evaluation of treatment response [7-12]. However, its diagnostic value at initial workup can be challenging for different reasons. First, FDG uptake by myeloma cells can be low because of variations in the glucose metabolism pathway [13]*.* Second, the depiction of skull lesions is generally hampered because of the high physiological FDG uptake of the brain [14]. Third, 18-FDG PET/CT can miss diffuse infiltration [12,15,16]. Therefore, whole-body MRI (WB-MRI) remains more sensitive than 18-FDG PET/CT for the initial diagnosis of MM [13].

Therefore, finding a radiotracer that could have superior diagnostic value at initial workup would allow for better discrimination of the initial tumor burden and hopefully also be useful to better evaluate the treatment response. Recent years have seen the advent of novel metabolic tracers such as 11C-methionine and 11C-labelled or 18F-labelled choline [17-19].

18F-choline, a tracer of phospholipids in the cell membrane, has good availability, as it is used for prostate cancer imaging. In a recent study, 18F-choline showed potential as compared to 18-FDG in MM, with about 75% more lesions detected in patients with MM with suspected relapsing disease [18]. 18F-choline has no physiological uptake in the brain, allowing optimal evaluation of the skull. Also, in this study, the median uptake of 18F-choline was superior to that of 18-FDG [18]. However, the retrospective design and heterogeneous population of this study warrant confirmation from prospective studies. Furthermore, as no reference standard was defined, the diagnostic performance of each modality could not be derived and compared.

Therefore, the current prospective diagnostic accuracy study was designed to compare, in patients with de novo MM, the number of bone lesions detected by 18-FDG PET/CT and 18F-choline PET/CT, with confirmation by a reference standard, in the entire body as well as in predefined skeletal areas (skull, spine, pelvis, ribs-sternum, superior limbs, inferior limbs).

## Methods

The scheme of the current prospective trial is shown in Figure 1, and the trial is described hereafter. Within a 21-day period, patients undergo 3 imaging procedures in the following order: 18F-choline PET/CT, 18-FDG PET/CT, and WB-MRI. The second and third imaging procedures will be performed 7 days ± 7 days from the previous procedure.

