#### Exclusion Criteria

Subjects will be excluded if they had any other cancer history in the previous 5 years or if they already had received myeloma treatment. To obtain optimal imaging assessments, we will exclude patients with uncontrolled diabetes, patients that had received injections of bone marrow stimulating growth factor <72 hours before proceeding to PET/CT or MRI, and patients that had received corticosteroids during the 7 days preceding PET/CT. Also, patients with MRI-incompatible implants will be excluded.

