## Discussion

### Overview

A recent study showed that the rate of false-negative results for 18-FDG PET/CT for the detection of bone disease in MM is about 10%, which could be attributed to a lower expression of hexokinase 2 [13]. A more sensitive tracer is therefore needed.

The role of 18F-choline in the management of relapsed prostate cancer is well-established, and it also has a role in the characterization of hepatocellular carcinoma. However, it remains poorly explored in the field of hematological diseases. 18F-choline is incorporated into the membrane of cells in division and could reflect the higher rate of neoplastic plasma cells.

A recent retrospective study has shown that 18F-choline detects 75% more focal bone uptakes than 18-FDG PET/CT [18]. However, this study was performed on a heterogeneous previously treated population with suspected progressive disease or relapse. It is known that 18-FDG metabolism in myeloma cells can change after first-line treatment and that FDG-negative myeloma cases at diagnosis can turn FDG-positive when they relapse [13].

This prospective comparative study of diagnostic accuracies will evaluate if 18F-choline PET/CT is superior to 18-FDG PET/CT in a homogenous population with de novo MM. The expected role (according to STARD 2015 definitions) of 18F-choline PET/CT is the replacement of 18-FDG PET/CT. The study has been designed to comply with QUADAS 2 guidelines. We will carefully exclude patients that are already being treated with corticosteroids because of the increased risk of false-negative findings on 18-FDG PET/CT and patients that had a recent injection of bone marrow stimulation factors because of the risk of a false-positive assessment of bone marrow on PET/CT and MRI [14]. Also, 18-FDG PET/CT, 18F-choline, and WB-MRI will be performed within a short time period to avoid misinterpretation due to the apparition of new bone lesions during the protocol.

By analyzing the number of bone lesions per skeletal area, we expect to find that 18F-choline is superior to 18-FDG PET/CT for the detection of bone lesions, especially in the skull, as 18F-choline has no brain uptake. A previous study showed that the median uptake of 18F-choline is higher than that of 18-FDG [18]. Hence, we expect that 18F-choline PET/CT will be more sensitive than 18-FDG PET/CT for the detection of focal bone lesions as well as for the detection of diffuse infiltration.

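### The fixed scan order (18F-choline, then FDG, then MRI) confounds tracer with time and with distance from the reference, and the scan windows can exceed the 21-day limit

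*Protocol article*

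**What the plan says.** The opening of Methods in the protocol article sets the scheme: "Within a 21-day period, patients undergo 3 imaging procedures in the following order: 18F-choline PET/CT, 18-FDG PET/CT, and WB-MRI". The next sentence adds that "The second and third imaging procedures will be performed 7 days ± 7 days from the previous procedure". The abstract repeats the overall limit: "Patients with de novo MM will undergo FCH-PET, FDG-PET, and whole-body MRI (WB-MRI) within a 3-week period". Neither place mentions randomising or counterbalancing the two PET scans.

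Exclusion Criteria bars patients "if they already had received myeloma treatment". For imaging quality it also leaves out "patients that had received corticosteroids during the 7 days preceding PET/CT"; a shorter look-back applies to "injections of bone marrow stimulating growth factor <72 hours before proceeding to PET/CT or MRI". The Discussion (Overview) explains that patients on corticosteroids are excluded "because of the increased risk of false-negative findings on 18-FDG PET/CT". It also says that the scans are kept close together so that lesions appearing during the protocol do not mislead the reading.

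Under Primary Outcome Measures, each lesion counted for either tracer is validated against whole-body MRI. PET lesions absent on MRI go to expert consensus. The Sample Size section compares the two counts with a Wilcoxon signed-rank test in 30 patients.

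**The concern.** The primary analysis is a within-patient difference, 18F-choline count minus FDG count. Pairing removes differences between patients but not differences between occasions. Because every patient has the scans "in the following order: 18F-choline PET/CT, 18-FDG PET/CT, and WB-MRI", anything that changes between the first and second PET enters that difference in full, and no analysis of the collected data can take it out again.

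Two further features add to this. First, the reference is acquired last, so 18F-choline is always the tracer further in time from the scan that confirms its lesions. Second, the permitted gap between the PET scans (up to 14 days) is longer than the steroid look-back (7 days), and the prior-treatment exclusion is worded as an entry criterion. The article itself names steroids as a cause of false-negative FDG scans. At stake is whether a difference in counts can be read as a property of the tracer.

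**Working it through.** **Inputs.** Overall limit 21 days (Methods; 3 weeks in the abstract). Two successive gaps, each 7 ± 7 days (Methods). Steroid look-back 7 days before PET/CT (Exclusion Criteria). Enrolment 8 of a planned 30 by June 2020 (Results and Sample Size).

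**1. Windows against the limit.**
- Each gap: 7 − 7 = 0 days to 7 + 7 = 14 days.
- First to third scan: minimum 0 + 0 = 0, nominal 7 + 7 = 14, maximum 14 + 14 = 28 days.
- Excess over the limit: 28 − 21 = 7 days.
- In whole days there are 15 × 15 = 225 gap pairs. Those summing to 22, 23, …, 28 number 7 + 6 + 5 + 4 + 3 + 2 + 1 = 28, or 12.4%. This counts permitted pairs; it is not a probability.
- If the 21 days is a binding cap, the maxima are 21 days from 18F-choline to MRI, 14 days from 18F-choline to FDG, and 14 days from FDG to MRI.

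**2. Steroid look-back against the PET gap.** Put 18F-choline at day 0 and FDG at day 14, which is allowed even under a 21-day cap if MRI follows within 7 days. The 7-day rule covers day 7 onwards. Steroids given after the 18F-choline scan and no later than day 6, that is 8 to 14 days before FDG, are not caught. Steroids continuing into the last 7 days are caught.

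**3. Direction of each route under the fixed order.**
- New lesions appearing over time: can be seen on FDG and not on 18F-choline. Favours FDG.
- Change before MRI: 18F-choline lies up to 21 (or 28) days from the reference, FDG up to 14. 18F-choline lesions are more exposed to going unconfirmed, partly offset by consensus. Favours FDG.
- Steroids or therapy between the two PET scans: 18F-choline is already acquired, so only the FDG count can fall. Favours 18F-choline.
- Therapy between FDG and MRI: affects confirmation for both tracers.

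The routes oppose one another, and the article gives no figure for any of them.

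**4. Illustration of the third route alone.** Every input here is an assumption: 30 patients, gamma-Poisson lesion burden with mean 17, detection probability 0.6 for both tracers, FDG detection reduced in k patients, 3000 replicates, two-sided 5% Wilcoxon test. Ranges are across runs and choices of gamma shape.
- k = 0: about 5% rejections.
- k = 3, 30% fall: about 6 to 7%.
- k = 5, 30% fall: about 10 to 11%.
- k = 8, 30% fall: about 19 to 21%.
- k = 8, 50% fall: about 30 to 37%.

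The model leaves out the two routes that favour FDG, so it shows sensitivity to one mechanism and does not estimate this trial's error rate.

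**The case against.** A reader might infer that elapsed time and interim treatment can only count against FDG. The documents do not support that. The time concern the article itself names is new lesions, which would help the later FDG scan, and the late MRI puts 18F-choline at the greater distance from the reference. This objection stands in full: the direction is undetermined.

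The 28-day figure can also be challenged. The 21-day sentence and the window sentence are adjacent and can be read together, with 21 days as an overall cap that 225 − 28 = 197 of the 225 gap pairs satisfy. That reading is reasonable, but the text does not state it, and a site could keep both windows and still exceed the limit.

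The treatment route is narrow. The steroid rule is tied to PET/CT and can be read as covering the FDG scan, so ongoing steroids are caught. The Reference Standard section calls all three scans baseline and sets them apart from later response to chemotherapy, which suggests imaging before treatment. The full protocol and Figure 1 are not shown and may bar treatment between scans, so the lack of such a sentence is not itself a fault. All this makes the route less likely. It does not close the gap between a 7-day look-back and a 14-day interval.

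Finally, the simulated rejection rates rest on unsourced inputs and model only harm to FDG. That is correct, and nothing in the conclusion depends on them.

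**Conclusion.** The point holds in limited form. The fixed order fully confounds tracer with scan order and with distance from the reference standard in the primary paired comparison; this follows from the stated design and needs no assumption. The net direction and size of any bias cannot be determined from the article. The windows permit up to 7 days beyond the stated limit unless the 21 days is meant as a cap, which is a mild inconsistency to reconcile. The steroid look-back leaves days 8 to 14 before FDG uncovered. Whether any patient falls there depends on practice that the article does not describe. This is an inexpensive improvement to make while most patients are still to be enrolled. It is not evidence that the trial is biased towards 18F-choline.

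**What to change.** - Reconcile the 21-day limit with the two scan windows and state which governs. Reconcile the steroid look-back with the permitted gap between the PET scans. Both choices are the sponsor's.
- Randomise which PET comes first for patients still to be enrolled: 30 − 8 = 22 at the June 2020 count.
- Add a sensitivity analysis of the primary Wilcoxon test, limited to patients who received no corticosteroid or myeloma therapy between scans and were imaged within the stated limit. This needs scan dates and any interim treatment to be on record.

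Cost: an amendment which, if judged substantial, needs an ethics committee opinion and agency authorisation under Amendments to the Protocol; some scheduling effort for tracer order; and one extra analysis. The trial would also have a mixed design, with the first patients all in one order, so randomising the rest reduces the confounding without removing it.

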**Figure 1 figure1:**
[figure not shown]
Flowchart of the current prospective diagnostic trial. CT: computed tomography; FDG: fluorodeoxyglucose; MRI: magnetic resonance imaging; PET: positron emission tomography.

### Patient Selection

#### Inclusion Criteria

Patients with a de novo diagnosis of MM as defined by the International Myeloma Working Group [20] will be prospectively and consecutively recruited at the University Hospital of Bordeaux. Patients must have quantifiable disease, either by the monoclonal component in blood or urine or by free light chain assay. Patients must be older than 18 years and be affiliated with the French social security regimen (or other health insurance regimen). Women of childbearing age must provide a negative pregnancy test before undergoing PET/CTs. Finally, protocol approval signed by the patient and the principal investigator must be obtained by the principal investigator before inclusion.

#### Exclusion Criteria

Subjects will be excluded if they had any other cancer history in the previous 5 years or if they already had received myeloma treatment. To obtain optimal imaging assessments, we will exclude patients with uncontrolled diabetes, patients that had received injections of bone marrow stimulating growth factor <72 hours before proceeding to PET/CT or MRI, and patients that had received corticosteroids during the 7 days preceding PET/CT. Also, patients with MRI-incompatible implants will be excluded.

### 18F-Choline PET/CT

#### Imaging Protocol

Patient must fast for 6 hours before the procedure. 18F-choline is injected with an activity of 3 MBq/kg. Whole-body PET/CT acquisition (from vertex of the skull to the knee) is performed 10 minutes after injection.

#### Interpretation Criteria

After anonymization, images will be independently read by two experienced nuclear medicine physicians, blinded from clinical data, biological data, and other imaging data performed during the protocol.

18F-choline has physiological uptake by the liver, spleen, pancreas, salivary glands, and urinary tract. Lymph node uptake will not necessarily be considered pathological, particularly in the mediastinum, as lymphadenitis and granulomatosis are sources of false positive findings. Any focal bone uptake will be considered pathological if the uptake is superior to that of surrounding background activity. The following 6 skeletal areas will be defined: skull, sternum-ribs, spine, pelvis, superior limbs, and inferior limbs. The number of focal lesions (FL), localization, and intensity of uptake (SUVmax) will be described for each skeletal area. Diffuse infiltration of the spine will be defined as diffuse spine uptake that is superior to liver uptake [11,14].

### 18-FDG PET/CT

#### Imaging Protocol

Patients must fast for 6 hours before proceeding to imaging. 18-FDG is injected with an average dose of 3 MBq/kg. PET/CT is performed from the vertex to the knees 60 minutes after injection.

#### Interpretation Criteria

After anonymization, images will be independently read by two experienced nuclear medicine physicians, blinded from clinical data, biological data, and other imaging data performed during the protocol.

18-FDG has physiological uptake by the brain, myocardium, kidneys, urinary tract, liver, and spleen. A focal bone lesion is defined as a focal uptake that is superior to surrounding background uptake. An extramedullary lesion will be considered if there is focal uptake within organ or lymph node structures. Of note, bilateral mediastinal lymph node uptake will not be considered as disease, as this will more likely correspond to granulomatosis lesions like sarcoidosis. The same 6 skeletal areas will also be used to classify focal bone lesions. The number of FL, localization, and SUVmax will be retrieved for each skeletal area. Diffuse infiltration will be defined as diffuse spine uptake that is superior to liver uptake [11,14].

### Whole-Body MRI (WB-MRI)

#### Imaging Protocol

WB-MRI examinations will be performed on a 1.5 Tesla device (Aera, Siemens Healthineers, Erlangen, Germany). First, the following imaging protocol will be applied: coronal T1-weighted turbo spin echo sequences on the pelvis (repetition time [TR] 785 ms; echo time [TE] 10 ms), coronal T2-weighted short-term inversion recovery (STIR) sequences on the pelvis (TR 13850 ms; TE 90 ms), sagittal T1-weighted turbo spin echo sequences on the spine (TR 453 ms; TE 12 ms), and sagittal T2-weighted STIR sequences (TR 7450 ms; TE 62 ms). Second, axial diffusion-weighted (DW) sequences will be acquired from the vertex to knees in 7 to 9 stacks. We will apply *b* values of 50 s/mm^2^ and 800 s/mm^2^. Each stack will be composed of 50 slices of 5-mm thickness (TR 7959 ms; TE 61 ms; inversion time 180 ms). Fused whole-body 3D maximal intensity projection of DW images will be built for analysis. The total length of the MRI protocol will be 45 minutes.

#### Interpretation Criteria

After anonymization, MRI images will be reviewed by two experienced radiologists blinded from PET/CT, clinical, and biological data. An FL is defined on coronal and sagittal sequences as a lesion with a diameter of more than 5 mm, with a low signal intensity on T1-weighted imaging and a high signal intensity on T2-weighted imaging. On DW images, an FL is defined as focal intensity above the bone marrow background signal. Diffuse bone marrow infiltration is defined based on previously published criteria [21]: a vertebral body to vertebral disk signal ratio <1.3 on T1-weighted images, vertebral body to psoas muscle signal ratio >2 on T2-weighted images, and vertebral body to kidney signal ratio >1 on DW images. A mild infiltration is defined as a pathological finding on T2-weighted or DW sequences. A moderate infiltration is defined as a pathological finding on both T2-weighted and DW images; a severe infiltration is defined as a pathological finding on both aforementioned sequences and on T1-weighted images.

